#### Stress Management and Behavioral Support

Within one week of initiating prehabilitation, a psychologist delivers a ~60-min psychoeducation session that focuses on stress management *via* relaxation, mindfulness, goal setting, and strategies to overcoming barriers to practice. In the week prior to surgery, participants are offered a second 60-min consultation with the psychologist to review their stress management experiences and provide further support for the acute perioperative period. To help participants with daily stress management practice, publicly available links to written and audio-based materials describing mindfulness, progressive muscle relaxation, deep breathing, and visualization are also provided.

#### Smoking Cessation

Participants that smoke are provided with information on the Canadian Cancer Society’s Smoker’s Helpline (www.smokershelpline.ca) for online programming and tools, as well as one-on-one counseling support. Smokers are also advised to speak to their local pharmacist and/or family doctor who can provide additional counseling, including education on the use of nicotine replacement therapy.

### Study Outcomes

Participant data to assess feasibility and derive estimates of effect are collected from the participants’ referrals, at the baseline assessment, within 1 week prior to surgery, and at 30 and 90 days postoperatively.

The total number of referrals and the rate at which they are received (per month) will be reported. To characterize the patients referred to the program, the following are collected from all referral forms (including usual care participants and those who decline research): referring surgical service; reason for referral; frailty level (*via* the Clinical Frailty Scale (3), embedded into the referral); cancer type; indicated surgery; referring healthcare practitioner type (*i.e.* physician, surgeon, clinic nurse, *etc.*), and participant demographics (age, sex, and general geographic location). The enrolment rate will be calculated as [# of enrolled participants]/[# of referred participants]. The frequency and reasons for declining participation in the study, declining prehabilitation (*i.e.*, usual care participants), and drop-out will be reported and compared using descriptive statistics of demographic and referral data.

Given the importance of scheduling and timing for prehabilitation relative to the date of surgery, several relevant time periods will be reported. The time from program referral to the date of surgery will be reported and is referred to as the ‘prehabilitation window’. We will also report the total preoperative period (time between consent for surgery and date of surgery) and prehabilitation duration (time from baseline assessment to surgery).

Reporting of the exercise prescription parameters and adherence to the programming will follow the Consensus on Exercise Reporting Template (62). Adherence to home and facility-based exercise sessions are recorded *via* attendance and standardized logbooks capturing training activity completed by the research coordinator. Adherence to stress management, nutrition plan, protein consumption, and utilization of smoking cessation tools (as required) is recorded weekly using a logbook within the participant manuals. Healthy eating practices advised by the dietitian are also assessed by a 3-day diet record in the week prior to surgery. Safety or adverse events related to prehabilitation are discussed during weekly communication between the participants and the research coordinator. Reporting and grading of adverse events will follow the Common Terminology Criteria for Adverse Events version 5.0 (63).

Estimates of program effectiveness are derived from a combination of patient-reported and functional performance measures, as well as clinical information from the medical record at each of the study timepoints. Aerobic functional capacity is measured using the Six-Minute Walk Test (6MWT) (64) and musculoskeletal functional capacity is assessed *via* grip strength using an isometric dynamometry (Jamar, Sammons Preston, Bolingbrook, IL, U.S.A.) according to established protocols (44). Body mass (kilograms) and height (meters) are measured using standardized procedures and are used to calculate body mass index (BMI, kg/m^2^). Body fat percentage, fat and fat free mass, impedance, resistance, and phase angle are recorded are measured *via* bioelectrical impedance analysis (mBCA 514, Seca, Hamburg, Germany) (65). HRQOL is measured using the 12-item Short Form Health Survey (SF-12) (66, 67) and the EuroQol 5 Dimensions 5 Levels (EQ5D-5L) (68) The Patient Health Questionnaire (PHQ-9) is used to assess depression (69). The EFS, PSS, and GLTEQ are also re-administered at each follow-up timepoint. Postoperative length of stay in number of days (including any readmissions) is recorded from the medical record. Complications, including mortality, are reported according to the Clavien-Dindo classification (70). All health events that require readmission will also be documented. Complication and health event data are extracted from the medical record at the 30^th^ and 90^th^ postoperative day for each participant.

Economic evaluation will be conducted from the perspectives of the individual and the hospital. Cost for an individual prehabilitation participant will be calculated on two fundamental components: the quantity of resources consumed and the unit cost of those resources related to prehabilitation. The EQ5D-5L will be used for the cost–effectiveness analysis as the health effect to determine the quality-adjusted life years (QALY) for the 90-day follow-up time period. The calculated participant costing and QALY will be used to determine the incremental cost–effective ratio (ICER). ICER will be calculated as a ratio of the difference in patient costing and the difference in QALY between FBP and HBP [ICER = (cost_FBP_ – cost_HBP_)_/_(QALY_FBP_ – QALY_HBP_)]. This will be calculated for both the program (measured cost for delivery of FBP and HBP) and patient perspective. Patient-perspective costing is measured by a patient-reported cost-diary that includes: direct healthcare cost (impact of the interventions on the use of healthcare services, such as visits to the general practice, specialist care, prescribed medication); direct non-healthcare costs (cost incurred by the patient and the family, such as cost of over-the-counter medication, cost of health activities, hours of paid and unpaid household help, transportation, and value of other out-of-pocket expenses, with specifics on exercise-related expenses); and indirect costs (value of productivity lost due to illness-related absence, including number of days absent from work, days lost from housekeeping, and other daily activities). A cost–impact from the perspective of the hospital will be conducted based on surgery-related hospital length of stay, readmission frequency, and length of stay of readmission(s) will be used to determine cost differences between those that participate in prehabilitation versus usual care participants. Cost impact will be estimated by applying the unit cost of an inpatient hospital day to the differences for participants that enrolled in prehabilitation and those that did not. Data from the Canadian Institute for Health Information on average cost of hospital stay will be used for the respective year.

In the second year of the study, prehabilitation participants will be asked to participate in semi-structured interviews conducted by telephone or in-person. The purpose of the semi-structured interviews is to capture insights about participant satisfaction, as well as the facilitators and barriers to prehabilitation engagement. To reach saturation for identifying meta-themes within a heterogenous population, a purposive sample of at least 15 participants per study arm will be sought to identify prevalent and salient themes related to study experiences. Qualitative content analysis will be conducted to identify barriers and facilitators for prehabilitation participation and engagement will be conducted using semi-structured interviews.

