#### Exercise

Each participant’s exercise prescription is developed and delivered by a kinesiologist and individualized to the results and observations obtained during the baseline assessment. Participants in both groups receive a moderate intensity aerobic and resistance training prescription to be completed 3–5 times per week for 60 min per session. Exercises specific to the anticipated locoregional impairments associated with the pending surgery are also prescribed for FBP and HBP participants to be completed independently. Participants in FBP are encouraged to attend two facility-based sessions per week where the aerobic training includes HIIT using the 10 × 1 protocol (51), and on such days, resistance training using the facility’s equipment is commenced after a 10 min rest period. All home- or community-based exercise sessions are supported with the provision of a stability ball, resistance bands, and a manual free of charge, and are intended to be completed independently (*i.e.*, unsupervised). Prior to initiating the exercise program, all exercises are instructed and demonstrated in the prehabilitation program facility where participants have an opportunity to practice and receive feedback/corrections or alternate exercises. The kinesiologist communicates weekly with participants by telephone to support program compliance, record adherence, appropriate progression, and to address any barriers to exercise that may prevent participation. Details of the aerobic and resistance training programs, as well as the locoregional impairment-based exercises are provided in **Tables 1** and **2**, respectively.

**Table 1 T1:** Exercise-based Total Body Prehabilitation.

	Home-based prehabilitation (HBP)	Facility-based prehabilitation (FBP)
Frequency	3–5 sessions per week (plus additional sessions for locoregional exercises as indicated)	
Intensity—Aerobic	MICT at 40–70% HRR or an RPE of 4–7/10	Home-based sessions are as per HBP. Facility-based sessions (twice weekly) employ the 10 × 1 HIIT protocol (10 cycles of exercise and recovery intervals, each interval is 1 min). During the first week, exercise intervals are 70–80% VO_2peak_ in session 1 and 75–85% VO_2peak_ in session 2 with recovery interval at a target an intensity of ≤50% VO_2peak_. In the second week and up to date of surgery, the exercise interval intensity target is set to 85–95% VO_2peak_.
Intensity—Resistance	2–3 sets of 8–12 repetitions at approximately 12–15 repetition maximum	

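### The FBP-versus-HBP ICER appears to set programme costs incurred before surgery against QALYs counted over the 90 days after it, so cost and effect horizons do not match

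*Protocol article*

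**What the plan says.** All statements are in the protocol article.

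- **Effect window.** The economic paragraph of Study Outcomes uses EQ5D-5L "to determine the quality-adjusted life years (QALY) for the 90-day follow-up time period". It does not name the day on which that period starts.
- **Ratio.** "ICER will be calculated as a ratio of the difference in patient costing and the difference in QALY between FBP and HBP". Two numerators are planned: "This will be calculated for both the program (measured cost for delivery of FBP and HBP) and patient perspective". The patient perspective uses a cost diary whose period is not given.
- **Assessment schedule.** Data are collected "at the baseline assessment, within 1 week prior to surgery, and at 30 and 90 days postoperatively". Effectiveness estimates come from "patient-reported and functional performance measures, as well as clinical information from the medical record at each of the study timepoints", so EQ5D-5L is due at all four points.
- **When the programme runs.** Delivery is preoperative. Table 1 (Exercise) sets the later HIIT intensity "In the second week and up to date of surgery". The dietitian and psychologist sessions fall in the first week and in the week before surgery. Study Outcomes defines programme duration as the interval from baseline assessment to surgery.
- **A second window.** The Analytic Plan models change in patient-reported outcomes starting at baseline and ending at day 90.

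**The concern.** A QALY is the area under a utility curve. In a cost-effectiveness ratio it should cover the same period as the costs. Here the delivery cost falls wholly before surgery, while the QALY period, read plainly, begins at surgery. The two modes differ in delivery during the preoperative weeks: supervised facility HIIT plus home sessions in FBP, home sessions only in HBP. A utility difference that builds up in those weeks would be paid for in the numerator and not credited in the denominator.

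The ICER is the only cost-effectiveness comparison of the two delivery models in the article, and it feeds the cost question RQ1j in Box 1. A reader choosing between models could be misled about cost per QALY, although the data for a matched horizon are already planned.

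**Working it through.** **Which window is meant?**

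1. Day 90 is postoperative in the assessment schedule, in RQ2a and RQ2b (Box 1), and in the extraction of complications.
2. Baseline to postoperative day 90 is not a 90-day period. It is 90 days plus a wait that varies by patient.
3. Ninety days counted from baseline matches no scheduled assessment.
4. The Analytic Plan states the baseline start explicitly; the economic paragraph does not.

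Surgery to postoperative day 90 is therefore the plain reading, but it is an inference.

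**What is lost on that reading?** The article gives no utility, cost, ICER or length of wait, so there is no figure to reproduce. What follows is illustrative. Assumptions:

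- D = FBP-HBP utility difference at the presurgical assessment, treated as the value at surgery. The difference is zero at baseline and grows linearly.
- T = days from baseline to surgery.
- d30 and d90 = the difference at days 30 and 90.
- The cost difference is the same in both ICERs.

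Trapezoidal areas in QALYs:

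- Preoperative = 0.5 × D × T / 365.25
- Postoperative = [0.5 × (D + d30) × 30 + 0.5 × (d30 + d90) × 60] / 365.25

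The postoperative area under three assumed courses, before division by 365.25:

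- Held to day 90: 30D + 60D = 90D
- Halved by day 30, zero by day 90: 22.5D + 15D = 37.5D
- Gone by day 30: 15D

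The postoperative-only ICER divided by the full-window ICER is (pre + post)/post = 1 + (T/2)/K, with K = 90, 37.5 or 15. D cancels.

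| T (days) | Held (K = 90) | Fading (K = 37.5) | Gone by day 30 (K = 15) |
|---|---|---|---|
| 14 | 1.08 | 1.19 | 1.47 |
| 28 | 1.16 | 1.37 | 1.93 |
| 56 | 1.31 | 1.75 | 2.87 |
| 84 | 1.47 | 2.12 | 3.80 |

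The omitted share of the full QALY difference, pre/(pre + post), runs from 7% (T = 14, held) to 74% (T = 84, gone by day 30).

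**Absolute size.** With D = 0.05, T = 28 and the fading course, the preoperative area is 0.5 × 0.05 × 28 / 365.25 = 0.0019 QALY. The postoperative area is 37.5 × 0.05 / 365.25 = 0.0051 QALY. The omitted amount is small, yet it is 27% of the total.

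**Dependence on the curve.** Take a difference of 0.03 at surgery and 0.01 at days 30 and 90. The postoperative area is (0.5 × 0.04 × 30 + 0.01 × 60)/365 = 0.0033. The preoperative area is 0.015 × T/365. The factors are 1.35, 1.44 and 2.05 for T = 28, 35 and 84. If the difference instead fell at once to 0.01 at surgery, the postoperative area would be 0.01 × 90/365 = 0.0025 and the factors 1.47, 1.58 and 2.40. The continuous curve is the more natural one, because the presurgical value starts the postoperative segment.

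**Direction.** The factor is 1 + pre/post. It exceeds 1 only if both areas have the same sign. With opposite signs it falls below 1, and it turns negative if the preoperative area is the larger.

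**The case against.** The strongest reply is that the start of the QALY period is not stated. The article refers to re-administering questionnaires at follow-up timepoints in a way that can include the presurgical visit, and the Analytic Plan starts patient-reported outcomes at baseline. If the QALY also starts there, nothing is omitted. This stands as a limit on certainty: a definite omission is not shown. It does not remove the point, because a baseline start does not fit a period described as 90 days, and the two sections would still need reconciling.

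A second reply is that a condensed article may leave QALY derivation to a fuller document. That is fair for the integration method. The window, however, is something the article does state, and as stated it does not match the delivery cost.

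A third is that a fixed postoperative window has the merit of equal length for every patient. That is a real trade-off and a reason to keep that result as a sensitivity analysis.

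A reader might also infer more than the document supports:

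- **That all preoperative quality-of-life gain is lost.** It is not. A gain common to both arms cancels in the difference, and a difference still present at the presurgical assessment can enter as the start of the postoperative curve. Only the between-arm area accrued before surgery is at risk.
- **That the ICER is certainly overstated, and by a large factor.** Size and sign rest entirely on assumed values; the low end of the range is 8%.
- **That the hospital cost-impact analysis is affected.** It uses no QALYs.

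**Conclusion.** The point holds as a minor one. On its plain reading, the economic paragraph gives the ICER mismatched horizons: delivery cost from baseline to surgery, effects from surgery to day 90. It also differs from the window that the Analytic Plan uses for patient-reported outcomes.

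Under waits of 14 to 84 days, equal utility at baseline, and differences of the same sign before and after surgery, the postoperative-only ICER would be about 1.1 to 3.8 times the full-window one. None of those inputs comes from the article, so the true size and direction are unknown. Longer waits enlarge the share at risk, and the article's COVID-19 section describes longer waits.

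The consequence is limited. The trial is a non-randomized pilot with feasibility as its primary objective, no decision rule rests on the ICER, and the article itself concedes limited precision.

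**What to change.** In the economic paragraph of Study Outcomes:

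1. State one horizon for costs and QALYs, from baseline assessment to postoperative day 90, and say that the patient cost diary covers the same period.
2. Compute the area under the curve from all four EQ5D-5L assessments at their actual dates.
3. Adjust the whole QALY difference for baseline utility, for example by measuring utility as change from the patient's own baseline throughout, or by regression on baseline utility. Adjusting only the preoperative segment would leave baseline differences between the self-selected arms in the postoperative one.
4. Report preoperative duration by arm and account for it in the comparison. Change from baseline alone is not enough: in the example above, a difference reaching 0.03 gives 0.015 × 28/365 = 0.0012 QALY over 28 days and 0.015 × 84/365 = 0.0035 over 84.
5. Show the surgery-to-day-90 ICER as a sensitivity result.
6. Reconcile the wording with the Analytic Plan.

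The cost is slightly more analysis work and a horizon whose length varies by patient. No additional EQ5D-5L assessment is needed. The diary needs changing only if it does not already cover the full period.

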## Methods

### Design

This is a pragmatic, preference-based, non-blinded, non-randomized trial to assess the feasibility and estimates of effectiveness of a clinically integrated, multimodal prehabilitation program for frail surgical oncology patients in an urban academic health center in Toronto, Ontario, Canada. Participant flow throughout the study is presented in **Figure 1**. The initial study protocol and subsequent amendments related to the COVID-19 pandemic have been approved by the University Health Network research ethics board.

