### Sample Size

A period of trial enrolment, rather than target sample size, was selected to inform expected rates of referral for a clinical service. The trial anticipates receiving 150 referrals for prehabilitation over 12 months. We estimate that one third of all referred patients will decline the intervention but will consent to making their hospital records related to their pending cancer surgery available for research (hereafter referred to as ‘usual care’ participants).

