### Analytic Plan

The analytic plan is described for prehabilitation implementation feasibility outcomes and exploratory analyses of prehabilitation effects. In line with comparative effectiveness research, presentation of confidence intervals will be emphasized for the purpose of accurately reflecting the actual data as well as directly addressing the uncertainty of the data. All quantitative analyses will be conducted in R (R Foundation for Statistical Computing, Vienna, Austria) and an alpha of.05 will be used.

Demographic and disease characteristics of all referred patients, as well as prehabilitation and usual care participants**’** will be summarized with appropriate parametric and non-parametric statistics. Reasons for ineligibility, declined participation in the study or intervention, as well as reasons for choosing FBP or HBP will be tallied. Group comparisons for referral information (surgical service, type of cancer, type of surgery, age, sex, and geographic location) will be assessed by one-way analysis of variance (ANOVA) for continuous and Chi-square test for categorical variables and described across FBP, HBP, usual care, and participants who decline participation. Baseline demographic and disease-related variables will be compared between study participants (FBP, HBP and usual care) ***via*** one-way ANOVA for continuous variables and Chi-square test for categorical variables.

Adherence to the interventions will be summarized dichotomously as meeting or not meeting the prescribed intervention components across each domain (exercise, nutrition, psychology, and smoking cessation). Reasons for deviations will be thematically categorized and summarized by frequency and percentage. Retention rates will be calculated as a total percentage of dropouts at the presurgical time point to the total participants enrolled for FBP and HBP. Reasons for dropout will be summarized using frequencies and percentage for each prehabilitation arm. Reported safety or adverse events will be summarized using frequencies and percentage for each group.

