## Discussion

As the evidence supporting prehabilitation for cancer surgery grows, questions about if and how it may be integrated into standard of care have followed. This protocol describes a study aimed at advancing implementation evidence to complement ongoing RCTs that target efficacy outcomes. Collectively, these will inform clinicians and researchers about the value and feasibility of clinically integrated prehabilitation for people with cancer. Importantly, to maximize generalizability to clinical care, as well a sustainable model of delivery, this study uses a referral-based enrolment strategy for a broad range of oncology patients who are identified as frail or vulnerable to adverse surgical outcomes. Related to our objectives of determining the appropriateness of referrals, a key learning outcome of our research will be the estimated frailty of referred patients using the Clinical Frailty Scale (3) and how those ratings correspond with other markers of frailty and performance, as well as prehabilitation adherence and study retention.

Within the context of a pragmatic trial design, we elected to offer two streams of prehabilitation, FBP and HBP, which are selected by participants using a shared decision-making strategy with a member of the research team. Advantages to the preference-based design include better motivation and compliance with an intervention, and subsequently more favourable experiences and outcomes than they may have in their non-preferred study arm (71). Moreover, preference for a study arm can enhance external validity and generalizability to clinical practice (72–75). In clinical settings, patients’ preferences, facilitators, and barriers to participation, intervention efficacy, and equitable access to services are fundamental considerations in designing and delivering health services and are core outcomes for implementation research (76–78). As such, offering both FBP and HBP options are likely to satisfy patients’ needs and capacities to ensure greatest benefit to all who are referred and examination of participation across study arms will yield novel and important insight into delivery models.

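### The ICER for facility- versus home-based prehabilitation is defined as a simple ratio of arm differences between self-selected groups, with no baseline adjustment or uncertainty method tied to it

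*Protocol article*

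**What the plan says.** The economic evaluation is described in the protocol article under Study Outcomes. EQ5D-5L is used "to determine the quality-adjusted life years (QALY) for the 90-day follow-up time period", and "ICER will be calculated as a ratio of the difference in patient costing and the difference in QALY between FBP and HBP". The formula is printed beside this sentence: cost in facility-based prehabilitation (FBP) minus cost in home-based prehabilitation (HBP), divided by the corresponding QALY difference. It is to be calculated from the program and the patient perspective. A separate hospital cost-impact analysis compares prehabilitation with usual care.

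Under Design, the study is a "pragmatic, preference-based, non-blinded, non-randomized trial". The Discussion says of the two streams that they are ones "which are selected by participants using a shared decision-making strategy" with a member of the research team.

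The Analytic Plan says that "presentation of confidence intervals will be emphasized". It compares baseline variables across FBP, HBP and usual care. It specifies mixed models for fitness, patient-reported outcomes and length of stay, Poisson regression for events, and a bootstrap of regression coefficients when there are outliers. None of these is linked to the ICER. Among the limitations in the Discussion, group differences due to self-selection are raised for the usual care comparison only.

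**The concern.** The people in the two arms will differ before treatment starts. The article itself names distance, travel cost and facility hours as obstacles to FBP, and it counts transportation in the patient cost. Some of what drives the choice of arm therefore also enters the numerator of the patient-perspective ICER.

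QALYs depend strongly on starting utility. If one arm begins with better utility and keeps part of that lead, the QALY difference contains it whether or not the intervention did anything. Over 90 days the denominator is small in any case, so a modest shift can multiply the ratio or reverse its sign. A negative ICER cannot be read alone, because it can mean either that FBP dominates or that it is dominated. When the denominator's interval spans zero, an ordinary interval for the ratio is not usable.

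At stake is the interpretation of the only cost-effectiveness ratio in the article. The primary feasibility objective is not affected.

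**Working it through.** The article states no ICER, EQ-5D standard deviation, cost difference or arm split, so there is no figure of its own to reproduce.

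**Inputs from the article.** Horizon 90 days. "The trial anticipates receiving 150 referrals for prehabilitation over 12 months", and "We estimate that one third of all referred patients will decline the intervention". This gives 150 × 2/3 = 100, so at most about 100 participants in FBP and HBP together.

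**Assumptions, not from the article.** Baseline utility imbalance 0.02 to 0.05; true QALY difference 0.002 to 0.010; cost difference 500 currency units; EQ-5D SD 0.15 to 0.25; within-person correlation 0.5 to 0.8; arm split from 50/50 to 20/80.

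**Step 1: ceiling.** 90/365.25 = 0.246 QALY at full utility throughout.

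**Step 2: shift in the QALY difference** = imbalance × 0.2464 if it persists, and half of that if it fades linearly to zero.

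| Imbalance | Persistent | Fading |
|---|---|---|
| 0.02 | 0.0049 | 0.0025 |
| 0.03 | 0.0074 | 0.0037 |
| 0.05 | 0.0123 | 0.0062 |

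**Step 3: effect on the ICER** = 500 / (true difference + shift). With a true difference of 0.005, the ICER without imbalance is 500/0.005 = 100,000 per QALY. A persistent imbalance (FBP minus HBP) gives:

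| Imbalance | QALY difference | ICER |
|---|---|---|
| +0.05 | 0.0173 | 28,868 |
| +0.03 | 0.0124 | 40,348 |
| −0.02 | 0.00007 | about 7 million |
| −0.03 | −0.0024 | −209,013 |
| −0.05 | −0.0073 | −68,303 |

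If the imbalance fades, −0.03 gives 500/(0.005 − 0.0037), about 383,000, and −0.05 gives 500/(0.005 − 0.00616), about −431,000.

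With a persistent imbalance, the sign reverses at an imbalance of (true difference)/0.2464 against FBP. That is 0.002/0.2464 = 0.008, 0.005/0.2464 = 0.020, or 0.010/0.2464 = 0.041.

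**Step 4: are such imbalances plausible?** The standard error of the baseline difference is SD × √(1/n1 + 1/n2). For 50/50 the root is 0.20, so the SE is 0.030 to 0.050. For 20/80 the root is 0.25, so the SE is 0.038 to 0.063. Across these cases, chance alone gives an absolute imbalance above 0.03 with probability 32% to 63%, before any self-selection.

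**Step 5: what adjustment achieves.** Simulation with 5,000 runs, 50/50 arms, SD 0.20, correlation 0.6 and a true gain of 0.0049 QALY for FBP:

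| FBP starts | Mean difference, unadjusted | Wrong sign | Mean difference, adjusted for baseline EQ-5D | Wrong sign |
|---|---|---|---|---|
| 0.03 lower | −0.0024 | 61% | +0.0020 | 37% |
| equal | +0.0051 | 27% | +0.0050 | 21% |
| 0.03 higher | +0.0123 | 8% | +0.0078 | 10% |

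With FBP 0.03 lower and SD and correlation varied over the assumed ranges, the wrong sign occurs in 58% to 66% of runs unadjusted and 18% to 43% adjusted. Adjustment pulls the mean towards the truth in both directions. Some bias remains because one baseline measurement captures only part of a persistent difference.

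**Step 6: remaining imprecision.** In the same simulation the SD of the estimated QALY difference is about 0.0085 unadjusted and 0.0063 adjusted. The 95% half-widths are 1.96 × 0.0085 = 0.017 and 1.96 × 0.0063 = 0.012. Both exceed the true 0.0049, so the denominator's interval would usually include zero even after adjustment.

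**The case against.** The strongest reply is that the printed formula only defines an ICER. It does not say that the differences are unadjusted, and regression-adjusted increments would fit it equally well. A condensed article may leave covariates, the bootstrap and net benefit to a fuller plan. This largely stands: a reader might infer that the plan commits to raw arm means, but the document does not say so. What remains is that the article prints the estimator, describes models and a bootstrap for other outcomes, and attaches none of them to this ratio. Followed as written, the formula gives an unadjusted comparison of self-selected groups.

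A reader might also infer that the ICER contradicts the emphasis on confidence intervals. It does not: that sentence is general, and nothing excludes an interval for the ICER.

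A third tempting reading is that the ICER would decide the delivery model. The article does not say this. Costs are one of ten feasibility questions in a pilot, and the economic work also includes a hospital cost-impact analysis.

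Finally, much of the instability is small-sample noise, and the Discussion already concedes low power. That is correct. Even with no imbalance the sign is wrong in 27% of simulated runs unadjusted and 21% adjusted. That concession concerns precision, however, and does not cover bias from patients' choice between FBP and HBP.

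**Conclusion.** The concern holds as a matter of specification. The ICER is given as a simple ratio of FBP–HBP differences, the arms are chosen by participants, and the article ties neither baseline adjustment nor an uncertainty method to it. The self-selection caveat does not extend to this comparison.

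A persistent imbalance of 0.02 to 0.05 shifts the QALY difference by 0.005 to 0.012 against a ceiling of 0.246. That is enough to change the ICER's size or sign when the true difference is of similar order. The horizon and the figure of about 100 participants come from the article. The imbalance, true effect, cost difference, SDs, correlation and arm split are assumptions, and the effect halves if the imbalance fades linearly.

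**What to change.** - State that incremental QALYs and incremental costs will be estimated by regression adjusted for baseline EQ5D-5L and a small prespecified set of baseline factors, such as age and Clinical Frailty Scale. The set should stay small, because there are at most about 100 participants with very mixed surgeries.
- Report incremental cost and incremental QALY separately with bootstrap 95% confidence intervals, and give a cost-effectiveness plane or net benefit alongside the ICER.
- Describe the FBP–HBP economic comparison as exploratory and subject to self-selection, extending the limitation already stated for usual care.
- As a sensitivity analysis, restrict to participants enrolled while both arms were open. Box 2 moves all exercise sessions to the home during the pandemic, so arm may be partly tied to calendar period. The article does not say whether virtual participants count as HBP.

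The cost is a change of wording and slightly more analysis work. EQ5D-5L is already collected at baseline, and age and frailty rating come from the referral form. Residual confounding and imprecision will remain.
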